##### Mental health complaints

Mental health complaints are operationalized as the six mental health complaints screened for (i.e., distress, need for recovery, alcohol use, depression, anxiety and posttraumatic stress disorder). These are measured as described above.

##### Absenteeism

Three items from the Productivity and Disease Questionnaire (PRODISQ) Module C are used to measure absenteeism from work. Absenteeism is operationalized as number of days on sick leave during the last three months and number of periods of sick leave during the last three months [65].

##### Work functioning

Work functioning will be measured by the NWFQ as described above.

##### Additional information on help-seeking behavior

Additional information concerning help-seeking behavior will be used as a secondary outcome measure, which includes 1) intention to seek help, assessed for the 11 formal help sources, 2) work as content of the consultation of various caregivers, 3) frequency of visits to the caregivers and 4) informal help-seeking behavior towards family or friends.

##### Work ability

Work ability will be assessed with the first item of the Work Ability Index (WAI) [66]. This item concerns the evaluation of current work ability compared to their lifetime best on an 11 point scale (0 = *completely unable to work*, 10 = w*ork ability at its best*).

##### Turnover intention

Turnover intention will be assessed by one item on plans to seek for a job outside of the present organization during the next year. The item can be answered on a dichotomous response scale (*yes, no*).

##### Wellbeing

Wellbeing is measured with three questionnaires measuring different concepts.

The Mental Health Continuum-Short Form (MHC-SF) is a 14-item self-report questionnaire on wellbeing in the categories 'languishing', 'moderate' and 'flourishing' [67]. The MHC-SF measures hedonistic wellbeing as well as psychological and social wellbeing. Participants rate the items on a 6-point scale (0 = *never*, 5 = *every day*). The MHC-SF has shown good internal consistency (> 0.80) and discriminant validity [68,69].

The WHO-5 wellbeing scale contains five positively formulated items on mental health. Participants are asked to rate the items using a 6-point scale (0 = *never*, 5 = *all of the time*). The WHO-5 has been validated in different populations with an acceptable internal consistency (Cronbach's alpha 0.84) [70].

The Utrecht Work Engagement Scale (UWES-9, short-form) measures engagement at the workplace. It is a 9-item scale, and items are scored on a 7-point rating scale (0 = *never*, 6 = *always*). Cronbach's alpha of the UWES-9 varied between 0.85 and 0.92 across 10 different countries, including the Netherlands [71].

##### Work productivity

Three items from the Productivity and Disease Questionnaire (PRODISQ) Module E are used to measure productivity losses due to presenteeism. The three items refer to the last work day, and they assess the amount of inefficient job performance, the quality loss of the work, and, if applicable, the reason for productivity loss [65].

#### Independent measures at baseline

As independent measures, we assess demographic characteristics, job characteristics and psychosocial work characteristics at baseline. Demographic characteristics, gender, age (in years), civil status (five categories), and ethnic background (three categories) will be assessed with self-formulated questions. As job characteristics, we will measure the occupation, nursing specialty (if applicable), work experience in years, work hours per week, and type of labor contract. Psychosocial work characteristics will include job demands, job control, social support at work from the supervisor, and social support at work from colleagues, which will each be measured by one self-formulated item on a visual analogue scale (VAS) (0 = *not*, 100 = *to great extent*). Additionally, one item will be added for conflicts at work with the supervisor or with colleagues. As possible prognostic factors for help-seeking behavior, we include gender [72-74], civil status [75], informal help-seeking towards family or friends [76], and previous experiences with mental health care, which is operationalized as having friends or family who were treated by a psychologist/psychiatrist at any time, or having been treated by a psychologist/psychiatrist himself/herself at any time [77].

#### Process indicators measured at three month follow-up

Process indicators for the feasibility evaluation of the WHS will be measured at three month follow-up (T1) and include 1) participants' compliance in both the OP-care and E-mental health arm; 2) participants' satisfaction; 3) adherence of OP to the protocol; and 4) satisfaction of OP. Participants' compliance will be assessed by objective data on response rate to the study, percentages of participants who made use of the invitation for an OP consultation or the e-mental health interventions (by track and trace); moreover, based on self-report data, the percentages of participants who followed the advice given by the OP or during the e-mental health intervention. Satisfaction of participants will be measured by self-report data on satisfaction with the provided feedback, satisfaction with the invitation for the OP consultation or the e-mental health intervention, satisfaction with the consultation by the OP or e-mental health intervention itself, and satisfaction with the advice given by the OP or given in the e-mental health intervention, including their perceived effectiveness. In the OP-care arm, protocol adherence of the OPs will be assessed by means of a checklist for each protocol step, which the OP has to fill out after each consultation with a participant of the WHS mental module. The OP's satisfaction and experiences with the WHS mental module will be assessed in a group interview after the three month follow-up.

#### Economic evaluation indicators at baseline, three month follow-up and six month follow-up

The cost-effectiveness of the WHS mental module will be assessed from a societal perspective. Differences in effect - job-specific impairments in work functioning - will be compared with differences in costs - costs due to intervention and health care and costs stemming from productivity losses in paid work.

The employer's perspective will be considered in a cost-benefit analysis by comparing the costs of occupational health care (including the WHS mental module) with the costs due to productivity losses in paid work. Health care utilization will be measured by the Trimbos/iMTA Cost Questionnaire for Psychiatric Illness (TiC-P) [61]. Questions on occupational healthcare utilization will be added to this questionnaire for the purpose of this study. The Productivity and Disease Questionnaire (PRODISQ) will be used to measure productivity losses due to absenteeism and presenteeism (inefficient job performance) [65].

#### Sample Size

##### Substudy 1

In a study by Isaaksson Ro [78] on help-seeking behavior in nurses with burnout, the formal help-seeking increased from 17% to 34%. Differences between the percentages of participants having sought formal help between the two study arms will be examined using a Chi-square test. For an increase of 17% with alpha = 0.05 (2-tailed) and a power of (1-beta) = 0.80, power calculation using the Nquery Advisor software results in 114 participants with mental health complaints for each of the two arms. Based on data from a prior study in this population ([name], [name], [name], [name], unpublished), we assume that 50% of the population will have impairments in either mental health, work functioning or both. Thus, for a comparison of workers screened positive in the control arm and the OP-care arm, 228 participants in each arm are necessary. Randomization will take place at the ward level; however, we do not expect any correlation between wards in the help-seeking behavior of their employees. Therefore, no inflation factor is used in the power calculation for Substudy 1 with the outcome measure help-seeking behavior. With an expected loss-to-follow-up of 10%, we must start the trial with N = 228/0.90 = 254 per condition at baseline.

##### Substudy 2

The trial is powered to detect a clinically significant effect, defined as at least 0.33 standard units when the (primary) outcome is transformed into a standardized effect size, also known as Cohen's d or the standardized mean difference. Lipsey and Wilson [79] conducted a second-order meta-analysis of psychological, educational and behavioral interventions and found that for these interventions, d = 0.33 to be corresponding with the lower bound of a medium effect size. We will conduct tests at alpha = 0.05 (2-tailed) and a power of (1-beta) = 0.80. Using Stata, it is shown that n = 145 per condition is required. For the primary outcome measure of this substudy, work functioning, no information on probable difference on ward-level exists. But as a precaution, we compensate for possible cluster effects introduced into the data because of randomization on ward-level. For cluster correction, we must multiply by a factor 1.3, which returns 145*1.3 = 189 per condition. Assuming a loss-to-follow-up of 10%, we must start the trial with N = 189/0.90 = 210 per condition at baseline.

In sum, the required minimum number of participants is 254 for the control arm, 254 for the intervention arm 2 (according to calculations for part 1) and 210 for the intervention arm 2 (according to calculations for Substudy 2); thus, in total, 718 participants are required for all three arms. We expect a response rate of about 45%; thus, 1596 employees must be invited to recruit the required 718 participants. As we will include 1731 employees, the source population is large enough to meet the needed sample size.

#### Statistical analyses

The baseline data and data of the primary and secondary parameters will be presented using descriptive statistics. The effectiveness of the intervention on the primary and secondary outcome measures will be analyzed on the employee level following the intention-to-treat-principle.

##### Effect evaluation

To study the effect on dichotomous outcome measures Chi-square tests will be used; thus, to test differences in proportions of subjects who score positive on the outcome measure between the study arms for each time of measurement. Change of proportion of employees in outcomes at follow-up (T1 and T2) will be analyzed using Generalized Estimated Equations (GEE), with wards and participants as cluster variables (where appropriate) and study-arm, time and their interaction (study-arm × time) as co-variates under the assumptions of an exchangeable working correlation matrix. Effects of demographic characteristics and prognostic factors on dichotomous outcomes measures will also be analyzed using Generalized Estimated Equations (GEE).

Effects of continuous outcome measures will be analyzed using multiple regression analysis. A multilevel analysis of variance will be conducted (GLM mixed models, repeated measurements), with ward as the primary hierarchical level and participants as the secondary hierarchical level (where appropriate). Effects of demographic characteristics and prognostic factors on continuous outcome measures will also be analyzed using multiple regression analysis.

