#### Primary outcomes measured at baseline, three month follow-up and six month follow-up

##### Substudy 1

The primary study parameter of the comparison between the OP-care arm and the control arm is help-seeking behavior. It regards formal help sources that the subject has used during the past three months. In the operationalization of formal help sources, 11 help sources are presented (i.e., psychologist, psychiatrist, general practitioner, OP, physiotherapist, supervisor, coach, in-company social worker, social worker, religious counselor, alternative therapeutic treatments). The list of help sources is developed in analogy with earlier studies on help-seeking behavior [61-64].

The outcome measure help-seeking behavior is dichotomized into 'did seek formal help' for participants who had made use of any of the 11 caregivers and 'did not seek formal help' if none of the 11 caregivers were visited.

##### Substudy 2

The primary outcome measure of the comparison of the E-mental health arm with the OP-care and the control arm is work functioning, operationalized as job-specific impairments in work functioning. It will be measured using a total score of the Nurses Work Functioning Questionnaire (NWFQ).

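### Substudy 1 tests its primary outcome at each follow-up and again by GEE with no deciding test named (about 7–10% error if both times are tested at 5%); Substudy 2 names no deciding contrast

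*Protocol article*

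**What the plan says.** All references are to the protocol article.

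- **Outcomes and times.** The outcome section is headed "Primary outcomes measured at baseline, three month follow-up and six month follow-up". Neither substudy has one follow-up singled out as primary. The Substudy 1 primary outcome is help-seeking, dichotomised as any or no use of 11 formal sources over the preceding three months. For Substudy 2, "The primary outcome measure of the comparison of the E-mental health arm with the OP-care and the control arm is work functioning", measured by the NWFQ total score.
- **Sizing, Substudy 1.** The Sample Size section describes a single test: "Differences between the percentages of participants having sought formal help between the two study arms will be examined using a Chi-square test". It names no time point. The calculation is "For an increase of 17% with alpha = 0.05 (2-tailed) and a power of (1-beta) = 0.80" and "results in 114 participants with mental health complaints for each of the two arms".
- **Sizing, Substudy 2.** "We will conduct tests at alpha = 0.05 (2-tailed) and a power of (1-beta) = 0.80", for a standardised difference of 0.33, giving 145 per condition.
- **Analysis of dichotomous outcomes.** The Effect evaluation section prescribes Chi-square tests "to test differences in proportions of subjects who score positive on the outcome measure between the study arms for each time of measurement". It then prescribes a GEE for the change at T1 and T2, with arm, time and their interaction, and with wards and participants as cluster variables where appropriate.
- **Analysis of continuous outcomes.** The same section gives multiple regression and a multilevel repeated-measures model with ward and participant levels. It states no separate test per time point.
- **Hypotheses.** The end of the Background section hypothesises that the two strategies are equivalent in their effect on work functioning.

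**The concern.** Substudy 1 is sized for one test, but its analysis section prescribes an arm comparison at each of two follow-ups plus a model covering both. Nothing says which result answers the primary question. If a significant result at either follow-up were read as success, the error rate would exceed the 5% used in the sizing.

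Disagreement between the results is also realistic, for two reasons:

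- **The two times measure different things.** Help-seeking looks back three months, and the occupational physician is one of the 11 counted sources. The OP-care section schedules the invited consultation within two weeks of the baseline questionnaire. The T1 window therefore contains that visit, while the T2 window covers only months three to six.
- **The two analyses differ.** The Chi-square test ignores wards; the GEE can take them into account. One may be significant and the other not.

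In Substudy 2 the gap is of another kind. One repeated-measures model serves two comparisons over two follow-ups, and the contrast that decides is not named.

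**Working it through.** **Step 1. Reproduce the plan's figures, to confirm that each substudy is sized for one 5% test.**

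Substudy 1: p1 = 0.17, p2 = 0.34, difference 0.17, mean 0.255, z = 1.960 (two-sided 5%) and 0.842 (80% power).

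- Without continuity correction: n = [1.960·√(2·0.255·0.745) + 0.842·√(0.17·0.83 + 0.34·0.66)]² / 0.17² ≈ 102.0, rounded up to 103.
- With continuity correction: (n/4)·[1 + √(1 + 4/(n·0.17))]² with n = 102.0 gives about 113.5, rounded up to **114**, the plan's figure.
- With 50% screening positive, 114/0.5 = 228. With 10% loss, 228/0.90 = 253.3, rounded up to **254**.

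Substudy 2: n = 2·(1.960 + 0.842)²/0.33² ≈ 144.2, rounded up to **145**. Then 145·1.3 = 188.5, rounded up to **189**, and 189/0.90 = **210**.

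All figures reproduce for a single two-sided 5% test at 80% power. Neither calculation allows for a second test.

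**Step 2. Substudy 1, both follow-ups tested at 5%.**

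The baseline comparison is not a claim of effect, so two tests count. If independent, the error is 1 − 0.95² = 9.75%. With correlation r between the T1 and T2 test statistics, it is the probability that either |Z| exceeds 1.96 under the null, obtained by simulation (1,000,000 draws). The documents give no r, so the range is an assumption.

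| r | P(at least one false positive) | multiple of 5% |
|---|---|---|
| 0 | 9.75% | 1.95 |
| 0.3 | 9.5% | 1.9 |
| 0.5 | 9.1% | 1.8 |
| 0.7 | 8.4% | 1.7 |
| 0.9 | 7.0% | 1.4 |

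The GEE is a further opportunity on the same data. It is not quantified here. The table also assumes that each single test holds its own 5%; whether an unclustered Chi-square test does so under ward randomisation is a separate matter.

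**Step 3. Substudy 2.**

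The numbers after loss are 189 in the E-mental health arm and 229 in each other arm (254·0.90 = 228.6). The shared arm gives the two comparisons a correlation of (1/189)/(1/189 + 1/229) = 229/418 = 0.55.

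- Two comparators, one difference test each: **8.9%** (1.8 times alpha).
- Two comparators with each follow-up also tested separately: 17.0% (r = 0), 15.8% (0.5), 14.6% (0.7), 12.4% (0.9), or 2.5 to 3.4 times alpha. The text does not state this set of four tests.
- E-mental health versus control only, with both follow-ups tested: 7.0% to 9.75%, as in step 2. With one deciding contrast it is 5%.

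**Step 4. After the change.**

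One deciding 5% contrast in each substudy restores 5% on the same sizing basis (114 and 145; 254 and 210 at baseline). By contrast, splitting alpha over two difference tests in Substudy 2 (0.025 each) would need 175 per arm: 175·1.3 = 227.5, rounded up to 228, and 228/0.90 gives 254 at baseline. Keeping 145 would leave 71.5% power.

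**The case against.** The strongest objection is that this is a condensed article. An order of tests or a multiplicity adjustment is commonly left to an analysis plan, which is not shown, so its absence is no finding. That stands, and the point does not rest on absence. The article itself states a rule of testing at every measurement, adds a second analysis of the same outcome, and sizes the substudy for one test. A later hierarchy would have to change or demote what is written here.

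A reader might go further and infer that every primary test is run at 5%, that success at any of them counts, and that the error is therefore two to three times alpha throughout. The document does not support this:

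- Per-time testing is written only for dichotomous outcomes. The NWFQ total is continuous and goes into a repeated-measures model, so four separate tests in Substudy 2 are a reading and not the plan.
- In Substudy 1 twice alpha is an upper limit, approached only when the two follow-ups are uncorrelated.
- Alpha appears only in the Sample Size section. That each follow-up is tested at 5%, and that either would count as success, is an inference from silence on the deciding test.
- A significant difference between E-mental health and OP-care would contradict the equivalence hypothesis, so it is not plainly a false positive claim of success.

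It may also be objected that making six months primary by default changes what Substudy 1 measures, because T2 recall omits the first three months and it is not shown that the assumed rise from 17% to 34% applies to the later window. This stands too: the time point is for the investigators to choose and justify.

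**Conclusion.** The point holds, at moderate size, and is firmest for Substudy 1. There the stated rule leaves the deciding time point and the deciding analysis open. Testing both follow-ups at 5% gives a false positive chance of about 7% to 10%, assuming a between-time correlation of 0.9 down to 0 and tests that each hold their nominal level.

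In Substudy 2 the defect is an unnamed deciding contrast. If both comparators were tested for difference without adjustment, the error would be about 9%. The 12% to 17% range is conditional on separate tests at both times and should not be quoted as the plan's error rate. If E-mental health versus control is the only difference claim and one contrast decides it, there is no inflation.

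This should be corrected. It does not undermine the design or the sample size.

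**What to change.** Before the data are seen:

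1. **Name one deciding contrast per substudy**, taken from the GEE with ward clustering (Substudy 1) and the multilevel mixed model (Substudy 2). It can be the arm effect at one follow-up, chosen and justified by the investigators, or a single joint test of the arm effect over T1 and T2. For help-seeking, the justification should say which three-month window is meant and how the invited consultation bears on it.
2. **Report the per-time Chi-square tests as descriptive only.**
3. **In Substudy 2, make E-mental health versus control the primary difference test.** Handle E-mental health versus OP-care separately, in line with its equivalence hypothesis, and not as the second step in a sequence of difference tests.

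Cost: a change of wording. Each substudy keeps one two-sided 5% difference test, so 254 and 210 per arm at baseline stay as they are. If the joint test is chosen, power should be restated, because the published calculation is for a simple two-arm comparison. The small downside is that an effect seen only at a non-primary follow-up becomes a secondary result.

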##### Cost-effectiveness evaluation

For the cost-effectiveness evaluation, the incremental cost-effectiveness ratio (ICER) will be calculated by comparing the differences in costs of health care utilization and productivity losses for each WHS strategy with the difference in effect on job-specific work impairments of both strategies. The index year for health care costs will be 2011. Productivity losses will be assessed using the human capital approach. Analyses will include cost-effectiveness planes and acceptability curves. Ancillary analyses (i.e., incremental net-benefit regression analysis) will identify subgroups of workers (e.g., participants with and without impaired work functioning or mental health) who derive particular benefit from the intervention.

In the cost-benefit analysis, the employer's perspective will be considered by comparing the costs of offering the WHS modules with the costs of productivity losses due to sickness absence (absenteeism) and working less efficiently while at work (presenteeism) for both WHS strategies separately.

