The objective of the Mental Vitality @ Work study is to study the effectiveness of two strategies for the WHS mental module in one cluster randomized controlled trial design with three arms. Substudy 1 aims to test the effectiveness of screening for problems in mental health and work functioning plus advice on appropriate interventions by an OP compared to a control group. It will study the effects on adequate help-seeking behavior, work functioning and mental health. We hypothesize that employees who receive the WHS mental module with screening plus an invitation for OP-care will show more adequate help-seeking behavior than employees in the control group. Furthermore, we hypothesize that work functioning and mental health problems will improve in employees who receive the WHS mental module with screening plus invitation for OP-care compared to employees in the control group.

Substudy 2 aims to compare the OP-care strategy with a second strategy, including the same screening of problems in mental health and work functioning as in the OP-care strategy plus a stepped care e-mental health approach. Substudy 2 will compare the effects of both strategies on work functioning and mental health. We hypothesize that both WHS mental module strategies are equivalent in their effectiveness on work functioning, mental health and wellbeing compared to the control group. An economic evaluation of the WHS mental module will be conducted alongside the randomized controlled trial. Cost-effectiveness of the WHS mental module will be assessed from a societal perspective. The employer's perspective will be considered in a cost-benefit analysis. Regarding cost effectiveness, we hypothesize that the WHS mental module with E-mental health interventions is more cost effective than the WHS mental module with OP-care.

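### The societal ICER has two different cost lists, one without intervention costs, and the analysis section names no control comparator

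*Protocol article*

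**What the plan says.** The protocol article describes the economic evaluation in two places.

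- **Economic evaluation indicators (under Measures).** The perspective is fixed: "The cost-effectiveness of the WHS mental module will be assessed from a societal perspective". The cost side of the comparison is "costs due to intervention and health care and costs stemming from productivity losses in paid work". Health care use comes from a questionnaire, and "Questions on occupational healthcare utilization will be added to this questionnaire for the purpose of this study". The employer analysis is described as "comparing the costs of occupational health care (including the WHS mental module) with the costs due to productivity losses in paid work".
- **Cost-effectiveness evaluation (under Statistical analyses).** The ICER is obtained by "comparing the differences in costs of health care utilization and productivity losses for each WHS strategy", set against the effect term "with the difference in effect on job-specific work impairments of both strategies". The employer analysis is now "comparing the costs of offering the WHS modules with the costs of productivity losses due to sickness absence (absenteeism") and presenteeism, carried out for each strategy on its own.

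The Background gives the hypothesis: "we hypothesize that the WHS mental module with E-mental health interventions is more cost effective than the WHS mental module with OP-care". It also expects the two strategies to be equivalent in effect. The Abstract (Discussion) and Impact of results look towards adopting the module in hospital occupational health services if it proves effective.

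**The concern.** The two sections describe the same societal analysis but list different costs. The section that tells the analyst how to form the ratio has the shorter list, and the item missing from it is the cost of the programmes under evaluation. A societal numerator without that item is incomplete.

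The omission need not fall equally on the two strategies. OP consultations may reach the numerator through the added occupational care questions. No corresponding cost item is named for delivering the e-programmes, whose use is tracked only as a process indicator. If that is how the data are captured, the omission works in the direction of the stated hypothesis.

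The analysis section also names no comparator. A single effect difference of both strategies, alongside a head-to-head hypothesis, reads most naturally as E-mental health against OP-care. That ratio ranks the two strategies. It does not say whether either is worth its cost compared with doing neither, which is the question an implementing hospital would ask. The employer analysis does not fill the gap, because it names no control contrast and its cost base differs between the two sections.

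**Working it through.** The article states no ICER, unit cost or willingness-to-pay value, so there is no figure to reproduce. The check is a comparison of the texts, followed by an illustration of direction.

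**Step 1. The texts side by side**

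| Item | Economic evaluation indicators | Cost-effectiveness evaluation |
|---|---|---|
| Intervention costs in the societal analysis | included | not named |
| Health care costs | included | included |
| Productivity losses | included | included |
| Control arm named as comparator | no | no |
| Employer cost base | all occupational health care, module included | offering the modules |

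The first and last rows disagree. The comparator is open in both sections.

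**Step 2. What the missing item does to the numerator**

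Let s be the screening cost, e the e-programme delivery cost and o the OP consultation cost, each per participant in the arm. Set all other cost differences to zero. Then

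full difference − stated difference = (uncaptured cost, E-mental health) − (uncaptured cost, OP-care).

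Assumed ranges, none of them from the documents: s = EUR 10 to 30 in each intervention arm, e = EUR 0 to 200, o = EUR 10 to 60.

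*Head to head, E-mental health minus OP-care.* Screening is the same in both strategies and cancels: (s + e) − (s + o) = e − o.

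- (a) OP visits captured, e-programme delivery not captured. Stated: −o, which is −60 to −10. Full: e − o, which runs from 0 − 60 = −60 to 200 − 10 = +190. The shift is e, or 0 to 200, and is never in favour of e-health. The sign changes whenever e exceeds o. With e = 50 and o = 10, −10 becomes +40. With e = 50 and o = 60, −60 becomes −10 and the sign holds.
- (b) Neither captured. Stated: 0. Full: −60 to +190. The omission could favour either arm.
- (c) Both captured. Only s is missing, and it cancels.

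*Each strategy against control.* Screening no longer cancels.

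- Under (a), the uncaptured cost is s + e = 10 to 230 for E-mental health and s = 10 to 30 for OP-care.
- Under (c), it is s = 10 to 30 for each strategy.

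**Step 3. From numerator to ratio**

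The ICER moves by the shift divided by the effect difference. The Background expects equivalent effects, so a head-to-head denominator may be close to zero. A modest omitted cost can then move the ratio a long way.

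**Step 4. Whether control can serve as comparator**

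Under Control group, that arm receives its results and e-health offer only at six months, when follow-up ends. The indicators section does not restrict cost collection to particular arms. Nothing in the design prevents a control contrast.

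**The case against.** The strongest reply is that a journal article compresses its text. The indicators section already defines the cost difference and names intervention costs first. The later sentence may be shorthand for it. The employer paragraph that follows refers to the cost of offering the modules, so delivery costs are expected to be known. This makes a deliberate exclusion unlikely. It does not remove the conflict: the sentence giving the calculation rule lists fewer components than the definition, and an analyst could follow either.

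A reader might infer that the two strategies will be compared only with each other. The documents do not go that far. The phrase about each strategy also fits each one against control, the Abstract mentions control data and cost-effectiveness in both intervention arms, and no section excludes control from the economic analysis. What stands is that no comparator is named.

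A reader might also infer that the ICER is biased towards e-health. That needs OP visits to be captured and e-programme delivery not to be. The added questionnaire items are not shown, and under (b) and (c) above the tilt is undetermined or absent.

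The planned cost-effectiveness planes, acceptability curves and net-benefit regression reduce reliance on an unstable ratio. They do not restore a missing cost.

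**Conclusion.** The point holds as an internal inconsistency and an unstated comparator. The two sections disagree on whether intervention costs enter the societal numerator, and following the analysis section literally omits them. The size cannot be determined from the article. On the assumed costs the omission can reverse the sign of the head-to-head cost difference, and it could favour E-mental health under one plausible pattern of data capture. If the ICER is head to head, as its wording most naturally suggests, it would not by itself support a decision to implement either strategy.

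Two further inferences are not supported. The first is that the employer analysis overstates benefit by the whole productivity loss seen under control: the text defines no benefit formula, so the contrast is unspecified rather than shown to be wrong. The second is that presenteeism costs double count the effect measure and call for a separate ICER without them: the work functioning questionnaire and the productivity items cover different content, and any overlap is not shown to be an error.

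The matter concerns the economic evaluation, not the primary outcomes. It should be corrected because it can change the ratio and costs little to settle.

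**What to change.** - Under Cost-effectiveness evaluation, use the cost list from the indicators section and spell out its parts: screening, OP consultation, e-programme delivery, other health care and productivity losses. State how OP visits made under the module are counted once, either as intervention or as health care use.
- State an incremental analysis over control, OP-care and E-mental health. It should include each strategy against control as well as the head-to-head contrast that the hypothesis needs.
- Use one cost base for the employer analysis in both sections, and express productivity loss as the difference between the strategy arm and control.

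The cost is a few sentences. No extra participant data are needed. Unit costs for screening and e-programme delivery must be obtained, but the employer analysis already requires the cost of offering the modules.
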